##### Video instruction

2.4.1.1

In the video, a patient shares her positive experience of using OLP to effectively reduce anxiety before surgery. This observational learning intervention via video builds on evidence supporting the beneficial effects of digital tools in surgical settings (41). Based on our knowledge of the role of self-efficacy as a contributor to the effects of OLPs (e.g., 43), the content of the video will be designed to enhance expectations of self-efficacy for coping with anxiety. This will also allow us to elucidate whether self-efficacy can be enhanced by observing others, resulting in more positive treatment expectations and perioperative health outcomes.

The patient in the four-minute video is played by a middle-aged woman matching the patient population (40–50 years old) sitting on a chair in a patient room. The patient talks about her experience and silent video sequences are shown of the anesthesia consultation, taking the placebo, the surgery preparation and her stay on the ward. The viewer sees how the patient takes the OLP pill and then relaxes. In the video, the patient again mentions the rationale of the OLP. She also explains her belief that she can influence her own situation with the OLP, reflecting self-efficacy as a mechanism underlying OLP effects.

#### Blinding

2.4.2

As expectation modulation is central to the study, blinding will be ensured as follows: randomization will be performed prior to informed consent by a study researcher who is not involved in the initial screening and enrollment. The random allocation sequence and concealment is ensured by sealed envelopes. Group allocation with respect to OLP administration will only be communicated to the study physicians who will explain the study objectives and obtain patient’s informed consent based on version A or B of the consent form. Therefore, as the study physicians are necessarily unblinded with respect to OLP administration, they are also blinded with regard to video observation. The study staff showing the video to the OLP+V-Group is not blinded in this respect, but otherwise have no contact with the patients and are not involved in their care. The nursing staff on the ward who administers the OLP is also not blinded to the administration of the OLP. They are only blinded regarding the video. The anesthesiologists and gynecologists involved in the regular perioperative patient care of all study patients are completely blinded to the groups. In addition, we use several strategies to ensure that patients do not exchange information with each other. Based on consultation with gynecology colleagues, we assume that only a limited number of patients per day at each center will meet the inclusion and exclusion criteria. In addition, we coordinate the distribution of patients on the wards with case management, and the overall short length of stay of women in the clinic makes communication between patients unlikely.

Entering the data into a database, pre-processing of the data and the initial quality control and descriptive analyzes are carried out prior to unblinding.

### Measures

2.5

#### Psychosocial characteristics

2.5.1

Prior to experimental procedures, participants complete a psychosocial questionnaire battery. For characterization of participants, we will focus primarily on sociodemographics, anxiety as a state and trait (short-form State-Trait Anxiety Inventory (STAI; 46, 47) and the general health status using the Pain and State of Health Inventory (SBI; 48).

#### Anxiety

2.5.2

Given the key role of anxiety in the experimental design of the PATE Trial, self-reported anxiety is measured using two different but complementary instruments: Preoperative Anxiety with the Numeric Rating Scale (NRS 0–10; 0 – No anxiety; 10 – Highest anxiety imaginable) and the Amsterdam Preoperative Anxiety and Information Scale (APAIS; 49, 50). This questionnaire consists of six items rated on a five-point Likert scale from “not at all” (1) to “extremely” (5). It represents the factors of anxiety and need for information regarding anesthesia and surgery. As a good indicator of its validity, this widely used questionnaire correlates with the State Anxiety Scale (STAI) with r=0.74, r=0.67 and r=0.64 and its retest reliability based on 42 subjects is r=0.92 for the anxiety scale and r=0.62 for the need for information scale (both p<0.001) (50). The brevity and clarity of this questionnaire made it particularly suitable for use in clinical settings where more complex questionnaires may not be acceptable to patients.

#### Expectations

2.5.3

In order to examine the overall treatment expectations and their interactions with the OLP, the expectations in relation to the anesthesia and operation are recorded using the Stanford Expectation of Treatment Scale (SETS; 51) and in relation to the OLP using the Generic rating scale for previous treatment experiences, treatment expectations (GEEE; 52). The SETS consists of items that specifically measure patients’ degree of optimism or pessimism about the expected effects of their treatment. These items are structured to capture a range of expectations, from certainty of benefit to concern about possible ineffectiveness, each rated on a Likert scale, allowing researchers to systematically assess the impact of expectations on clinical outcomes before surgery (53). The GEEE assesses patients’ expectations of their specific treatment, in this case OLP. The scale includes measures of positive and negative expectations, previous experience with similar treatments, and the current effects of the treatment under investigation. It uses NRS to assess expectations of improvement and possible side effects. This comprehensive but brief approach provides a nuanced understanding of how patients’ expectations and previous experiences may influence their treatment outcomes in clinical settings (54, 55). Expectations are measured repeatedly to capture the impact of the study physician’s suggestions regarding the OLP and of the video.

#### Postoperative pain

2.5.4

Postoperatively at T4 and T5, patients indicate their pain at rest and during movement (NRS 0–10; 0 – No pain at all; 10 – Highest pain imaginable). In addition, based on previous studies (23, 56), patients rate their pain based on localization, which includes “deep abdominal pain,” which is described as dull, cramping, and difficult to localize, and is indicative of visceral pain, usually from internal organs. In contrast, “superficial wound/scar pain” is described as somatic pain, which is typically more localized and associated with the skin, muscle or connective tissue around the surgical wound or suture (both assessed on Visual Analogue Scales (VAS 0–10; 0 – No pain; 10 – Highest pain imaginable). Furthermore, we record the subjective perception of pain relief and satisfaction with the pain therapy using the NRS.

#### Patient perspective

2.5.5

In order to capture the patient’s perspective beyond their ratings of anxiety and pain, we examine attitudes towards the acceptability of OLPs as well as perceived characteristics of the doctors. For the latter, patients rate the perceived warmth and competence of the study physician in the consultation and of the anesthesiologists performing anaesthesia postoperatively, using 6 items each for warmth and competence (57). Each item is rated on a 5-point scale from 1 (not at all) to 5 (extremely).

To deepen our understanding of the patient perspective on the use of OLPs in the future, patients are asked postoperatively about the appropriateness and potential use of placebos. For this purpose, patients rate the appropriateness of taking a placebo before surgery on an NRS (NRS 0–10; 0 – Not appropriate; 10 – Very appropriate). We also measure self-efficacy, the extent to which an individual is confident that they have contributed to improve their preoperative well-being. Patients also give their opinion on whether they would consider taking a placebo in a similar or different situation in the future.

#### Healthcare providers perspective

2.5.6

Furthermore, we are interested in the acceptability of OLPs by healthcare providers. The healthcare providers are asked about their view on anxiety reducing effects in the treated patient after the administration of the OLP assessed with an NRS (NRS 0–10; 0 – No effect; 10 – Very good effect).

#### Clinical data

2.5.7

In order to analyze the effects of our intervention on objective measures such as medication requirements and medication intake, we record:

previous illnesses, previous medication the preoperative consumption of sedativesmedication administration and dosage (including hypnotics and analgesics) during induction of anesthesiamedication, especially analgesics in the recovery room and in the post-operative phase

In addition, we record the type of surgery and times relevant in everyday clinical practice with regard to the duration of anesthesia induction, the operation and in the recovery room, as well as the length of hospital stay.

### Data management

2.6

Both project coordinators (authors [name] and [name]) are part of the Collaborative Research Center 289 “Treatment Expectations”, which is responsible for conducting studies at both the Hamburg-Eppendorf and Essen sites. A standardized data protection concept was created for all projects of the Collaborative Research Center and the approval of the data protection officer of the University Medical Center Essen and the University Medical Center Hamburg-Eppendorf was obtained for further subprojects.

Apart from patient consent and the key pseudonym list, all data is exclusively pseudonymized, i.e. encrypted using a numerical code and stored accordingly. The participants are assigned a corresponding numerical code, which is used to identify questionnaires and electronic data.

The patients receive the questionnaire battery mainly in digital form on a tablet, but in paper form right before the induction of anesthesia and in the recovery room. To avoid losing data, we prefer the digital solution, but it’s not possible to use tablets immediately before surgery and in the recovery room, so patients are asked by staff and it’s documented on paper. For this, the open-source survey tool LimeSurvey (LimeSurvey GmbH, Hamburg, Germany) is administered by a central project of the CRC (58). Only the study investigators have access to the data ([name] and [name]). As the study is conducted collaboratively by two study physicians at only two already cooperating study centers within the CRC 298, no data monitoring committee is necessary.

### Data analysis

2.7

A power analysis calculated with G*Power (version 3.1.9.6) resulted in a sample size of 120 patients for an expected small to medium effect size f of 0.2, two measurement time points, three groups, a significance level of α=0.05 and a power of 0.95. In order to be able to take possible exclusions during the course of the study into account, 20% more patients will be recruited, so that the final sample size is N=144 women. The effect size was derived from our own data and the literature after careful consideration with experts and colleagues at the two university hospitals. A medium to small effect size was chosen in order to be able to investigate small effects.

To analyze the main outcome (object 1), preoperative anxiety (APAIS), we will perform a univariate analysis of variance (ANOVA) with *post hoc* tests to determine differences in anxiety before surgery in the three groups. To analyze the dynamic changes of anxiety in the different groups before and after open placebo administration (TAU, OLP and OLP-V), repeated measures analyses of variance followed by *post hoc* tests are performed (object 2). In addition, ANOVAs will be conducted to assess postoperative pain (NRS) and other clinical characteristics by group (object 3). Patient and staff reports are primarily analyzed descriptively and free-text qualitatively (object 4). Furthermore, correlation and regression analysis will be used to identify exploratory predictive patient characteristics (object 3 & 4). No interim analysis is planned. If data is only available from one patient at three or fewer time points, the patients are excluded from the analysis.

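### The 95% power comes from a two-time-point calculation, but the primary test is a one-way ANOVA; whichever scale f = 0.2 is on, the sample-size paragraph contradicts itself

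*Protocol article*

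**What the plan says.** Section 2.7 (Data analysis) gives the sample-size basis. The calculation was done in G*Power and arrived at "a sample size of 120 patients for an expected small to medium effect size f of 0.2, two measurement time points, three groups". Alpha was set at 0.05 and the target power at 0.95. Adding 20% brings recruitment to 144. The choice of f is justified thus: "A medium to small effect size was chosen in order to be able to investigate small effects".

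The same section then states the primary test: "To analyze the main outcome (object 1), preoperative anxiety (APAIS), we will perform a univariate analysis of variance (ANOVA"), followed by post hoc tests between the three groups. Repeated-measures ANOVA appears only for objective 2, the course of anxiety over time. Section 3 (Anticipated results, Objective 1) confirms that the primary comparison is of APAIS across the three arms immediately before surgery. No baseline covariate or repeated factor is stated for it.

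The article names neither the G*Power procedure nor a correlation between the two measurements.

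**The concern.** A one-way ANOVA on a single occasion has no place for a number of time points, so the power statement describes a different test from the one assigned to the primary outcome. This matters because f does not mean the same thing in the two tests. In a repeated-measures interaction it is scaled to the group-by-time effects; in a one-way ANOVA it is scaled to the spread of group means on one occasion.

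At stake is how the primary result will be read. If f = 0.2 was meant for the primary comparison, a null result would be taken as 95%-powered evidence against a small-to-medium effect when the chance of detecting one was about even. If f = 0.2 was an interaction effect, the trial was sized for a large difference between arms while telling the reader that it can look for small ones. Objective 1 also asks whether the video adds to OLP. That contrast between two arms rests on the post hoc tests, and the article states no power for it.

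**Working it through.** **Inputs.** From section 2.7: N = 120 (144 after inflation), f = 0.2, k = 3 groups, m = 2 time points, alpha 0.05, power 0.95. From section 2.3: block randomization for balance, taken here as 1:1:1, so 40 per arm. Assumed, because not stated: the correlation rho between the two measurements. All powers use the noncentral F distribution with noncentrality lambda, in G*Power's parameterisation.

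**Step 1. Reproduce 120.** For the within-between interaction, lambda = f² × N × m / (1 − rho), with df 2 and N − 3.
- rho = 0.4: lambda = 0.04 × 120 × 2 / 0.6 = 16.0, power 0.952. The smallest balanced N reaching 0.95 is 120.
- rho = 0.3: N = 141. rho = 0.5: N = 102.

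Other candidates:
- Repeated-measures between-group effect, lambda = f² × N × m / (1 + rho), df 2 and N − 3. The best case is rho = 0: lambda = 9.6, power 0.788 at N = 120, and 198 patients are needed for 0.95. Any positive rho makes it worse.
- One-way ANOVA: 390 patients are needed (step 2).
- Within-subject time effect: 120 corresponds to a rho of about 0.27, but this test does not compare arms.

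So the interaction is the only one of these tests of a difference between arms that returns 120, and it needs an unstated rho of about 0.4.

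**Step 2. Reading A: f = 0.2 describes the group means in the primary ANOVA.** lambda = f² × N, df 2 and N − 3.
- N = 120: lambda = 0.04 × 120 = 4.8, power 0.476.
- N = 144, all analysed: lambda = 5.76, power 0.556.
- N for 80% power is 246; for 95% it is 390.
- At N = 120 the detectable f is 0.287 (80% power) or 0.363 (95% power).

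**Step 3. Reading B: f = 0.2 is on the interaction scale.** Suppose the arms are equal at the first occasion and deviate from the overall mean by e at the second. The interaction effects are then +e/2 and −e/2, so the interaction f is half the one-way f at the second occasion. Interaction f = 0.2 therefore corresponds to a one-way f of 0.4. For the primary ANOVA, lambda = 0.16 × 120 = 19.2 and power is 0.979. This f is twice the value that the article calls small to medium, and large by the usual convention.

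**Step 4. Contrasts between two arms (pattern of means assumed).** Two-sided t-test, 40 per arm, alpha 0.05 without multiplicity correction, one-way f = 0.2:
- Equally spaced means: adjacent arms differ by f × √1.5 = 0.245 SD, power 19%.
- Both OLP arms equal: OLP differs from TAU by f × 3/√2 = 0.42 SD, power 47%.

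Under reading B with equal spacing, adjacent arms differ by 0.4 × √1.5 = 0.49 SD (power 58%), and TAU differs from OLP+V by 0.98 SD.

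**The case against.** The strongest reply is that the two values of f are on different scales, so it is wrong to take a 95% figure for an interaction and set 48% for a one-way test beside it. That stands. A reader might infer that the primary test simply has 48% power. The article does not support this, because it does not say which scale f = 0.2 is on; if it is the interaction scale with equal baselines, the primary test has 98% power for the corresponding effect. The reply does not rescue the paragraph, since that effect is then no longer small to medium.

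Second, the interaction and its correlation of 0.4 are inferred, not stated, and a condensed article may leave both to the full protocol. That also stands, and their absence is not the fault raised here. The mismatch is visible without them: the sizing uses two time points and the primary test uses one.

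Third, the limitations section (4.1) already concedes that smaller effects may go undetected and that an approach other than ANOVA may be sensible. This tempers the claim about small effects but does not disclose that the stated power and the primary test do not match. Nor would adjusting for baseline close the gap under reading A. With lambda = 0.04 × 120 / (1 − rho²), df 2 and 116, and an assumed rho of 0.5 to 0.7, power is about 60% to 78%.

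Fourth, the article predicts the largest effect in the OLP+V arm but gives no spacing of means in its text. The contrast figures are therefore illustrations, as labelled.

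**Conclusion.** The point holds in conditional form. The sample size comes from a calculation with two time points, and the primary analysis is a one-way ANOVA on one occasion. Either f = 0.2 refers to that ANOVA and its power is 48% at 120 patients (56% at 144) instead of 95%, or f = 0.2 is an interaction effect and the trial is sized for a one-way f of 0.4, which contradicts the article's own description of the effect. The 48% needs only the stated f, N and alpha and equal arms. The 98% also needs equal baselines. The attribution to an interaction needs an assumed correlation near 0.4.

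A reader might also infer that the G*Power run was wrong, or that the trial must grow to 390 patients. Neither follows. The figure of 120 is attainable for an interaction, and the 390 applies only under reading A with 95% power retained as the target.

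**What to change.** Rewrite the sample-size paragraph in section 2.7 for the test that will be run, naming the test and the scale of f. For example: *With 120 evaluable patients in three equal groups, the one-way ANOVA of APAIS has 48% power at f = 0.20, 80% at f = 0.29 and 95% at f = 0.36 (two-sided differences between arms, alpha 0.05).* If the interaction calculation is kept as background for objective 2, state its correlation and say that it does not describe the primary test.

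Delete the sentence about investigating small effects. Add the power for OLP versus TAU and for OLP+V versus OLP, with the assumed pattern of means labelled as an assumption; the two patterns in step 4 would serve.

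The cost is a rewording and a stated power that may be less favourable. No added patients and no change in trial conduct are requested.

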### Design and groups

2.3

The study design of this bicentric, prospective, randomized, controlled, interventional trial is visualized in **Figure 1**, and procedures are described in detail in subsequent sections. Female patients are randomized into three groups before undergoing gynecological laparoscopic surgery. Randomization is accomplished prior to the personal interview with the study physician. To randomize the patients, we use block randomization with random distribution to ensure a balance in sample size across groups over time and the ability to perform interim analysis. Stratification is performed within the Hamburg and Essen clinic locations.

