### Study procedures

2.4

Patients undergoing elective gynecological laparoscopy at the University Hospitals of Hamburg and Essen are offered to participate in the study. After consultation with an anesthesiologist who is not involved in the study, patients are informed about the study, clinically examined and informed consent is obtained by a study physician, an experienced anesthesiologist. In all groups, information about the study is provided by the study physicians in the premedication outpatient clinics individually, which is typically one to five days before the surgery at both study sites.

Patients are assessed at 5 predefined time points. After informed consent, patients complete a comprehensive questionnaire battery (T1). This package includes information on demographics, state and trait anxiety, pain level over the past 4 weeks, treatment expectations regarding to the upcoming surgery and, if applicable, expectations concerning OLP (for details see 3.5). Patients will complete a short questionnaire at the beginning and at the end of the consultation with the study physician, about their current anxiety and treatment expectations in order to assess the impact of the study physician’s suggestions, including the rationale for OLP. Additionally, the patients rate the warmth and competence of the study physician using a standardized questionnaire. Patients in the OLP+V-Group watch the video after the consultation with the study physician and are also subsequently asked to answer questions about their perception of the video.

At the time the patients are called to the operating room, approximately 45 minutes before the start of surgery (T2), patients randomized to the OLP groups receive OLPs from the nursing staff. In addition, the patients evaluate their preoperative anxiety. Just before the induction of anesthesia in the preoperative phase (T3), preoperative anxiety is assessed again. In addition, the anesthetist subjectively assesses the patients’ level of calmness or anxiety. After surgery in the recovery room, patients are asked about their current level of anxiety and about their current pain level for visceral and somatic pain modalities (T4).

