A well-known problem in OLP trials is the need for unblinding, which is not an easy obstacle to overcome in OLP trials that require communication of the rationale. However, all other parts of the trial are single-blinded and all healthcare professionals performing the standard medical procedures are double-blinded. Although we have developed a guideline for communicating the rationale for OLP, we cannot rule out the possibility of slight variations in patient conversation resulting in differences in the effect of OLP administration. In addition, confounding cannot be excluded due to the bicentric design with different procedures and different gender of the study physicians at the two study centers, although the bicentric design is also a strength. To minimize possible differences, all procedures are standardized and controlled to the greatest possible extent. Because we cannot rule out the possibility that the study physician’s attitude towards open-label placebos may have an influence on the outcome, we minimize the time spent by the study physician and the patient in consultation only to the study enrollment and OLP instructions, and secondly we capture the patients’ perspective on the perceived characteristics of the physicians (see 2.5.5.). Furthermore, the power analysis was not designed for conducting further subgroup analyses and possibly smaller effects cannot be recorded. The calculation of an ANOVA does not take random effects into account, so it may make sense to use a different statistic approach. The postoperative situation in particular may also depend on the clinical outcome of the surgery, resulting in smaller effects not being detectable.

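### The primary ANOVA names neither a baseline anxiety covariate nor site; a prespecified ANCOVA would use data already planned, for a gain that depends on an unstated correlation

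*Protocol article*

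**What the plan says.** All references are to the Protocol article.

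- **Primary analysis (2.7 Data analysis).** For preoperative anxiety on the APAIS, "we will perform a univariate analysis of variance (ANOVA", followed by post hoc tests across the three groups. No covariate or site factor is named for Objective 1 here or in section 3. Repeated anxiety ratings enter only the repeated-measures ANOVA for Objective 2.
- **Baseline data (2.4 Study procedures).** On the T1 questionnaires: "This package includes information on demographics, state and trait anxiety". Section 2.5.1 identifies the instrument as a short-form STAI. APAIS at T1 is not named. Current anxiety is also rated at the beginning and end of the consultation with the study physician.
- **Stratification (2.3 Design and groups).** "Stratification is performed within the Hamburg and Essen clinic locations".
- **Correlation (2.5.2 Anxiety).** Of the APAIS: "this widely used questionnaire correlates with the State Anxiety Scale (STAI) with r=0.74, r=0.67 and r=0.64".
- **Site (4.1).** "confounding cannot be excluded due to the bicentric design with different procedures and different gender of the study physicians". The same section adds that procedures are standardised as far as possible, and that an approach other than ANOVA might be sensible, without choosing one.
- **Sample size (2.7).** The calculation takes "an expected small to medium effect size f of 0.2". The design entered into it is "two measurement time points, three groups". With α at 0.05 and a target power of 0.95 it led to 120 patients, raised to 144.

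**The concern.** Patients differ in how anxious they are before they enter the trial. In an ANOVA on one post-randomisation score, all of that variation sits in the error term. A covariate that predicts the preoperative score removes part of it and also corrects chance imbalance at 40 to 48 patients per arm.

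Site raises a related issue. When allocation is balanced within site but site is left out of the model, any site difference stays in the error term and the standard errors tend to be too large. The authors stratify on site and expect that sites may differ, so the analysis should reflect it.

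The loss matters more here because the sample size was computed for two measurement times, while the primary test uses one. That test draws no benefit from within-patient correlation unless a baseline is put into the model.

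**Working it through.** **Inputs.** f=0.2, three groups, α=0.05, N=120 and N=144 (2.7). Equal allocation is assumed. It is also assumed that f=0.2 describes the spread of group means on the single preoperative score. The correlation r between covariate and outcome is not given for trait anxiety, so it is varied.

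**Step 1: the plan's own figure.** For a group-by-time interaction with two measurements, λ = f²·N·2/(1−ρ) with 2 and N−3 degrees of freedom. The article does not state ρ. With ρ=0.5 the required N is 102. With ρ=0.40 it is 120: λ = 0.04×120×2/0.6 = 16.0, power 0.952. So 120 is reproduced only under an assumed ρ of about 0.40, and for a repeated-measures test. The figure of 144 is 120×1.2.

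**Step 2: the primary test as named.** For the one-way ANOVA, λ = f²·N with 2 and N−3 degrees of freedom.
- N=120: λ = 0.04×120 = 4.80, power 0.476.
- N=144: λ = 0.04×144 = 5.76, power 0.556.
- Power 0.95 would need 390 patients.

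**Step 3: ANCOVA with baseline anxiety and site.** λ = f²·N/(1−r²) with 2 and N−5 degrees of freedom. In this step site is charged its degree of freedom but credited with no explained variance.

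| r | λ, N=120 | Power, N=120 | λ, N=144 | Power, N=144 |
|---|---|---|---|---|
| none (ANOVA) | 4.80 | 0.476 | 5.76 | 0.556 |
| 0.2 | 5.00 | 0.493 | 6.00 | 0.574 |
| 0.3 | 5.27 | 0.515 | 6.33 | 0.599 |
| 0.4 | 5.71 | 0.550 | 6.86 | 0.636 |
| 0.5 | 6.40 | 0.602 | 7.68 | 0.689 |
| 0.7 | 9.41 | 0.779 | 11.29 | 0.854 |
| 0.8 | 13.33 | 0.908 | 16.00 | 0.953 |

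Power 0.95 requires r of about 0.84 at N=120 or 0.80 at N=144. The two degrees of freedom cost almost nothing: with r=0 the power at N=120 is still 0.476.

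**Step 4: site alone.** With a share s of variance explained by site, λ = f²·N/(1−s). At N=120, s=2% gives power 0.484 (0.8 points more) and s=10% gives 0.520 (4.4 points more).

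**Step 5: which covariate is safe.** Randomisation precedes consent (2.4.2). The consent form differs by arm, and version B presents the placebo as a means to reduce anxiety (2.4.1). T1 follows consent (2.4). T1 state anxiety may therefore already reflect allocation, and adjusting for it could remove part of the effect. Trait anxiety is taken at the same visit; using it assumes that a trait scale is hardly moved by the consent wording. The start-of-consultation rating would qualify only if it precedes all arm-specific information, which the article does not make clear.

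**The case against.** The strongest reply is that this is a condensed article, that covariates are often left to an analysis plan, and that the word univariate refers to one dependent variable and does not exclude covariates. Section 4.1 also leaves room for another method. Part of this stands: if the analysis plan already contains these terms, only the article's wording needs to be brought into line. But the article does name a model for the primary outcome, with group as its only stated term, and the remark in 4.1 commits to nothing.

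A second reply is that this concerns efficiency and not error. That stands. A reader might infer that the primary analysis is biased or invalid. It is not: comparing randomised arms without adjustment is unbiased, and omitting a stratification factor tends to be conservative.

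A third reply concerns size. A reader might put the reported 0.64 to 0.74 into the formula and expect power of 0.71 to 0.83 at N=120. Those values relate APAIS to the STAI State scale. They are not given for trait anxiety, for an interval of one to five days, or expressly for the short form. They are an optimistic guide only, and a gain of 2 to 4 points (r of 0.2 to 0.3) fits the article equally well.

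Nor is adjustment the only way to gain power without more patients. A planned one-degree-of-freedom linear contrast, assuming equally spaced means in the order postulated in section 3, has power 0.584 at N=120 and 0.664 at N=144 at the same f, with no covariate.

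**Conclusion.** The point holds as a worthwhile improvement to a valid but inefficient primary analysis. The gain comes almost entirely from baseline anxiety and depends on r. For r from 0.2 to 0.7 it is about 2 to 30 percentage points at either sample size, and the article does not show where in that range trait anxiety lies. Site adds under 1 point if it explains 2% of variance and about 4 points at 10%; its place in the model rests on matching the stratified randomisation.

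Two stronger conclusions are not supported. Adjustment does not restore the stated 0.95 power unless r is about 0.8 or more; it recovers part of the gap. And site is not a source of lost power comparable to baseline anxiety. All power figures assume equal arms and that f=0.2 applies to the single preoperative score.

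**What to change.** For Objective 1, replace the ANOVA with a prespecified ANCOVA of preoperative APAIS anxiety on arm, site and STAI trait anxiety. Report adjusted arm differences with 95% CIs. Add or substitute a state or current anxiety rating only if it is collected before the patient receives any arm-specific information. Fix the covariates before unblinding, so that the choice cannot depend on results. State the assumed r and the power of this model at N=120 and N=144.

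The cost is a change of wording and two degrees of freedom, with no new data for the trait-anxiety version. Moving a state rating ahead of the arm-specific consent would be a change of procedure and is not needed for the basic fix.
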